## Abstract

**Background:**

Students in the United States spend a meaningful portion of their developmental lives in school. In recent years, researchers and educators have begun to focus explicitly on social and emotional learning (SEL) in the school setting. Initial evidence from meta-analyses suggests that curricula designed to promote SEL likely produce benefits in terms of social-emotional competence (SEC) and numerous related behavioral and affective outcomes. At the same time, there are often barriers to implementing such curricula as intended, and some researchers have questioned the strength of the evaluation data from SEL programs. As part of the effort to improve programming in SEL, this paper describes the protocol for a cluster randomized trial of the ACT OUT! Social Issue Theater program, a brief psychodramatic intervention to build SEC and reduce bullying behavior in students.

**Objective:**

The objective of this trial is to examine if a short dose of interactive psychodrama can affect SEC metrics and bullying experiences in schoolchildren in either the short (2-week) or medium (6-month) term.

**Methods:**

The ACT OUT! trial is a cluster randomized superiority trial with 2 parallel groups. The unit of measurement is the student, and the unit of randomization is the classroom. For each grade (fourth, seventh, and 10th), an even number of classrooms will be selected from each school—half will be assigned to the intervention arm and half will be assigned to the control arm. The intervention will consist of 3 moderated psychodramatic performances by trained actors, and the control condition will be the usual school day. Outcome data will be collected at baseline (preintervention), 2-week postintervention (short term), and 6-month postintervention (medium term). Outcomes will include social-emotional competency; self-reported bullying and experiences of being bullied; receptivity to the program; and school-level data on truancy, absenteeism, and referrals to school displinary action for bullying. A power analysis adjusted for clustering effect, design effect, and potential attrition yielded a need for approximately 1594 students, consisting of an estimated 80 classrooms split evenly into intervention and control arms.

**Results:**

This study was funded in June 2019; approved by the Indiana University Institutional review board on September 17, 2019; began subject recruitment on November 5, 2019; and prospectively registered with ClinicalTrials.gov.

**Conclusions:**

Many states have issued recommendations for the integration of SEL into schools. The proposed study uses a rigorous methodology to determine if the ACT OUT! psychodramatic intervention is a cost-effective means of bolstering SEC and reducing bullying incidence in schools.

**Trial Registration:**

ClinicalTrials.gov NCT04097496; https://clinicaltrials.gov/ct2/show/NCT04097496

**International Registered Report Identifier (IRRID):**

PRR1-10.2196/17900

## Introduction

### Social-Emotional Learning and Bullying

In the United States, students typically spend 1224 hours each year at school (6.8 hours per day for 180 days/year) [1], which is a substantial portion of their developmental lives. In this context, the past 25 years have seen renewed calls for the US education system to focus on holistic child development and social and emotional learning (SEL) in addition to standardized academic metrics [2]. SEL is widely considered to be important for improving students’ academic and nonacademic outcomes [3]. The implementation of SEL curricula, and even the core definition of SEL, does vary somewhat [4], and researchers continue to design and test SEL programs and implementation approaches in educational settings, typically using a framework advanced by the Collaborative for Academic, Social, and Emotional Learning (CASEL), which focuses on 5 domains: self-awareness, self-management, social awareness, relationship skills, and responsible decision making [5]. Learning in these domains is expected to foster corresponding social-emotional competence (SEC) [6]. A model from a recent study (*Conceptual Model for Advancing SEL in Schools*) by Greenberg et al [7] proposed that an overall interaction between SEL and SEC domains and program implementation leads to the improvement of various short-term and long-term outcomes for students. Although individual study results have varied considerably, an examination of 4 meta-analyses of hundreds of SEL studies in the US education system found substantive evidence for short-term benefits across a wide spectrum of outcomes, including targeted SEC outcomes, improved academic performance, reduced problematic conduct frequency, and lower emotional distress. Longer-term outcomes were significant in 2 meta-analyses for academic achievement [8].

Importantly, these positive outcomes appear in some cases to extend to serious school-related behavioral issues, such as bullying. Bullying is relatively ubiquitous in US schools. The prevalence of school bullying reported in a 2014 meta-analysis of 80 studies that included data on youth aged 12-18 years was 35% for traditional bullying and 15% for cyberbullying [9]. Thus, it is notable that several studies have observed an association between SEL programs and/or constructs and the attenuation of bullying or aggressive behavior [10-12], and an inverse relationship exists between perceptions that SEL instruction is being offered and perceptions of bullying at school [13].

Although best practices for SEL education have been proposed and are being refined, there remain many barriers to implementation. These include costs related to training and teachers’ time to learn about and teach SEL curricula, perceived inability to divert instructional time to SEL, potential lack of fidelity due to selective use of manualized elements, and competition with academic testing time [14,15]. For some SEL curricula, teacher time comprises a large fraction of the measured cost [16], although accurate measurement of costs and benefits of a given SEL curriculum is complex and subject to meaningful variability [17]. In addition, some scholars have been critical of the level of rigor of many SEL and SEC studies [18], asserting that the positive findings from meta-analyses may be overestimated or that the speed of SEL program adoption may exceed the generation of knowledge and understanding of how to maintain positive outcomes [19]. The current state of knowledge suggests the continued importance of research into SEL programming, both as an outcome (ie, development of SEC through SEL) and as a mediator of problem behavior (eg, bullying). To advance what is known, SEL research should prioritize methodological rigor and approaches that minimize school resource costs.

### The Proposed Study

This study will be an assessment of the ACT OUT! social issue theater program as a universal SEL intervention targeting SEC and bullying in elementary, middle, and high school students. ACT OUT! is an existing program that has been performed in various forms by professionally trained members of an acting ensemble since 1995 [20]. The present iteration consists of 3 distinct 15-min scenarios per grade range (elementary, middle, and high) that present age-appropriate improvisational dramas that illustrate issues related to SEL and bullying, including facilitated discussion between the actors—who remain in character—and the students. The program lasts approximately 1 hour to fit within a typical class period within the school day, including introductions, performance, and engagement.

ACT OUT! may be contrasted with typical SEL curricula. SEL curricula tend to consist of manualized, structured classroom or multicomponent programs involving multiple sessions over time. The median number of sessions within an SEL program in a meta-analysis of 213 SEL studies was 24 [21]. Being 1 hour in duration, ACT OUT! is substantially shorter and is performed by third party, professional actors, thus meeting the goal of reduced school resource costs for SEL programming but potentially raising concerns about if such a relatively brief dose could reasonably be expected to produce an effect. Underlying this study is a supposition that unique properties of a dramatic performance may specifically trigger SEL responses. In Aristotle’s *Poetics*, which is the first known work on dramatic theory, it is written that a dramatic tragedy (in the Aristotelian sense) is designed to arouse certain feelings, “wherewith to accomplish catharsis of…emotions” (as cited in an academic essay by Rosenstein [22] from a translation by Richard McKeon). This precise mechanism underlies the development of psychodrama as a psychotherapeutic intervention, as combined action and verbalization can present a situation that elicits an emotional response “freed from the restricting stereotyped residues of past experience” [23]. Recent studies and meta-analyses have examined psychodrama as a means of prevention and/or behavior change with generally positive findings [24-30]. Researchers have also found that youth are receptive to psychodramatic elements as part of a larger prevention curriculum [31]. However, no published studies have measured any outcomes of a single-session psychodramatic SEL experience.

This will be the first study to examine if a short dose of interactive psychodrama can affect SEC metrics and bullying experiences in schoolchildren in either the short (2 weeks) or medium (6 months) term. To respond to recent criticism of SEL studies, we have chosen to utilize the SPIRIT 2013 clinical trial guidelines in developing this protocol to promote rigor, reproducibility, and transparency [32].

## Methods

### Ethics Approval and Consent to Participate

This study was granted approval by the Indiana University institutional review board (IRB; #1908563296).

### Trial Design

The ACT OUT! trial is designed as a proof-of-concept cluster randomized superiority trial with 2 parallel groups. Although the unit of measurement is the student, the unit of randomization is the classroom, stratified by school. For each grade (fourth, seventh, and 10th), an even number of classrooms will be selected from each school; half of the selected classrooms will be randomly assigned to the intervention arm and the other half will be assigned to the control arm. If there is an odd number of classrooms for a given grade and school, the excluded classroom will be determined randomly. The use of this approach will better ensure comparable sociodemographic and school-level factors between intervention and control arms. Study hypotheses and objectives are shown in Figure 1. Participant flow, including measurement points, is shown in Figure 2.

**Figure 1 figure1:**
[figure not shown]
Hypotheses and objectives.

**Figure 2 figure2:**
[figure not shown]
Participant timeline. GPA: grade point average; TAU: treatment as usual.

### Choice of Comparators

The comparator in this study is treatment as usual (TAU), which in this case reflects continued school activity as would have otherwise occurred. This study uses a novel and low-dose intervention in a protocol that would, in a clinical setting, approximate an early phase II stage. As a result, the core questions revolve around if the intervention works at all versus if it is superior to other mechanisms that may impact the same metrics. This is consistent with recent recommendations from an expert panel from the National Institutes of Health [33].

### Study Setting

The ACT OUT! trial will be conducted in public and charter schools in Marion County, Indiana, an urban county of 954,670 people who are 54.8% non-Hispanic white, 28.9% African American, and 10.6% Hispanic, with a median household income of US $44,689 [34]. The trial will recruit schools until meeting a threshold of 80 classrooms, 40 randomized to the intervention condition and 40 parallel classrooms randomized to the control condition.

### Eligibility Criteria

#### Inclusion Criteria

Participating classrooms must comprise fourth-grade (elementary), seventh-grade (middle), or 10th-grade (high) students. Single grades within each academic level were chosen to reduce variability that might be introduced by different age and maturity ranges when interpreting effects within levels. For elementary and middle school levels, the second-highest grade level was selected. For high school, 10th grade was selected because mandatory school attendance in Indiana ends at age 16, potentially introducing bias at the level of school enrollment for grades 11 and 12.

#### Exclusion Criteria

If a given grade within a school has an odd number of classrooms, 1 classroom will randomly be excluded from participation. Participants and their parents or legal guardians will review the study procedures. This study will utilize a waiver of active parental consent (see Recruitment section), and so parents or guardians may opt out on behalf of their dependents, and participants may opt out themselves.

### Intervention Delivery Qualifications

All individuals delivering the psychodrama interventions will be professional actors trained to the standards of Claude McNeal Productions, a professional theater company.

### Intervention

Eligible classrooms will be randomized to attend a 1-hour ACT OUT! interactive, semi-improvisational psychodrama performance or to continue with their school day as normal (TAU). Interventions will be delivered within the standard school day as defined for each classroom and school. The ACT OUT! production will include 3 vignettes paired with moderated discussions between the audience and the actors, and the latter will remain in character for the duration of the intervention. Intervention guidelines will be made available alongside the published study.

### Intervention Adherence

Adherence to the ACT OUT! intervention protocol will be measured at each delivery point using a fidelity checklist by a part-time employee of Claude McNeal Productions who is not a member of the acting ensemble. The fidelity checklist will contain scenario-specific items for all potential scenarios and will be made available as a multimedia appendix attached to the primary outcomes paper. Given the nature of improvisational psychodrama, the checklist will identify core areas and themes that must be addressed for the specific intervention to be considered to have been delivered with fidelity to the model. Each content area or procedure will be identified as *delivered/complete* or *undelivered/incomplete*, and the ratio will be used to generate a fidelity percentage for each delivery instance. To establish reliability, a second individual from the research team will attend 15% (6/40) of performances and complete fidelity checklists to compute interrater reliability (free-marginal kappa).

### Outcomes

#### Primary Outcomes

##### Overall Social-Emotional Competence at the 2-Week and 6-Month Posttests

SEC will be measured using the scaled variable generated by the Delaware Social-Emotional Competency Scale [35]. This scale reflects 4 of CASEL’s 5 core domains of SEC and has an established internal consistency coefficient of 0.84 in a large representative sample of youth. Furthermore, its developers demonstrated measurement invariance across grade levels, race, ethnicity, and gender [35]. This instrument provides an aggregate rating for overall SEC but cannot be used to generate separate scales by CASEL domains.

##### Self-Reported Bullying Behavior and Self-Reported Experiences of Being Bullied at the 2-Week and 6-Month Posttests

Bullying behavior and experiences of being bullied will be measured using the Bullying and Cyberbullying Scale for Adolescents (BCS-A), which uses 2 parallel 13-item scales [36]. This instrument includes items assessing physical, verbal, relational, and cyber bullying and was found in the development study to explain variance in adolescent problems beyond previously established tools—the Olweus Global Bullying Scale [37] and the Forms of Bullying Scale [38]—while displaying concurrent validity. The BCS-A also collects ratio rather than ordinal measures of bullying, which allows for face-valid use of the instrument for different time frames. As such, although the original BCS-A asked about a time frame in the past 3 months, this study will ask about a time frame in the past 2 weeks to match study protocols.

##### Referrals to Discipline for Bullying at the 6-Month Posttest

Referrals to discipline related to bullying will be obtained from school records in aggregate by cluster.

#### Secondary Outcomes

##### Student Receptivity to the ACT OUT! Intervention

This will be measured at the 2-week posttests using an instrument based on work published by Dent et al [39], which measures the degree to which adolescents find the event to be enjoyable, interesting, a waste of time, boring, understandable, difficult to understand, believable, important, and helpful, each on a 4-point ordinal scale.

##### Social-Emotional Competence Subdomains for Seventh- and 10th-Grade Students

The SEC subdomains of social awareness, emotion regulation, relationship skills, and responsible decision making will be measured using scales from the Washoe County School District Social-Emotional Competency Assessment [40]. These scales have established reliability and validity demonstrated through a unique multiyear, multimethod study, although the methods utilized did not produce traditional reliability values [40]. These items will not be collected from fourth-grade students because they would substantially increase the length of the survey instrument.

##### Truancy/Absenteeism and Academic Performance at 6-Months Postintervention

These will be assessed using objective data obtained from school records in aggregate by cluster.

### Sample Size

The sample size was calculated based on the primary outcome (change in SEC). Notably, there are no extant studies examining the effects of professionally acted interactive psychodrama on SEC outcomes and, hence, no directly applicable effect size estimates. However, several studies have utilized psychodrama/theater as an intervention component for non-SEC outcomes, including health promotion, sexual abuse prevention, HIV prevention, violence prevention, and nutrition education. Those studies found widely varying, significant effect sizes ranging from small to large, and, in cases where effect size calculations were not included, significant improvements in outcome metrics were found. The interventions varied substantially in quality, scope, and relationship with the measured outcomes [24-29]. An earlier Cochrane review covering the years 1990 to 2006 found only 9 studies of inconsistent quality, with generally modest but positive results [30]. Separately, a robust 2012 meta-analysis by Sklad et al [41] related to SEC identified 31 universal school-based programs that addressed social learning with an aggregated Cohen *d* of 0.70 (SE of *d* 0.10), a large effect size, but those programs were longer than the ACT OUT! intervention.

On the basis of this information, we have powered this trial to detect a moderate difference in SEC (Cohen *d*=0.30). For a baseline sample with a parallel superiority trial, with a 2-sided significance of .05, power of 0.80, and location of the mean in 1 group as a percentile of the other group set at 62% (corresponding to Cohen *d*=0.30), we calculated a need for 340 participants. As this is a cluster trial, we adjusted for similarities within the groups (clustering effect) using previous research on smoking prevention [42] as a conservative metric in the absence of similar data for SEL. This yielded an intracluster correlation (ICC) value of 0.153. The design effect, assuming 20 students per classroom (*m*), was calculated as [1+(m−1)×ICC], yielding 3.907. The design effect multiplied by the number of participants was 1328, but we also wanted to plan for approximately 20% loss to issues related to matching and attrition. Thus, we calculated a final sample need of 1594 students, constituting an estimated 80 classrooms evenly split into intervention and control arms.

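### The 20% loss allowance was applied as ×1.2 instead of ÷0.8, so 1594 students cover a loss of about 16.7%, not 20%

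*Protocol article*

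**What the plan says.** The Sample Size section of the protocol article builds the figure in three steps.

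1. The basic size is set "with a 2-sided significance of .05, power of 0.80", with the effect entered as the "location of the mean in 1 group as a percentile of the other group set at 62" percent, which the article equates with Cohen d = 0.30. From this, "we calculated a need for 340 participants".
2. With 20 students per classroom and an intracluster correlation of 0.153, the design effect is 3.907, and the size becomes 1328.
3. For losses, "we also wanted to plan for approximately 20% loss to issues related to matching and attrition". The section ends: "Thus, we calculated a final sample need of 1594 students", "constituting an estimated 80 classrooms evenly split into intervention and control arms".

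The formula for the third step is not written out. The Methods paragraph of the Abstract repeats the result: the power analysis "yielded a need for approximately 1594 students".

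**The concern.** An allowance for a proportion lost has to be worked backwards from the number that must remain. If 20% of those enrolled are lost, 80% remain, so enrolment must be the required number divided by 0.8. Adding 20% of the required number gives a smaller figure, because the loss then also applies to the added students. The stated 1594 looks like the second calculation.

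The allowance matters here because the article itself, under Limitations, warns that an unexpectedly large share of students may prove unmatchable, particularly at 6 months. The loss margin is the plan's numerical protection against that risk, and it is smaller than stated.

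**Working it through.** **Inputs, all from the Sample Size section:** two-sided alpha 0.05; power 0.80; effect at the 62nd percentile; 1:1 allocation; 20 students per class; ICC 0.153; loss about 20%.

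**Reproducing the plan's chain**

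- Effect: the standard normal quantile at 0.62 is d = 0.3055.
- Basic size: a two-sample t-test at this d needs 169.2 per arm, rounded up to 170, so 340 in total. This matches the plan exactly. (The normal approximation gives 338.)
- Design effect: 1 + (20 − 1) × 0.153 = 3.907. This matches.
- After clustering: 340 × 3.907 = 1328.4, stated as 1328. This matches.
- Loss step: 1328 × 1.2 = 1593.6, rounded to 1594. This matches. Division gives 1328 / 0.8 = 1660, which does not.

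So every step reproduces, and the last one only as a multiplication.

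**What 1594 delivers**

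- Remaining after a 20% loss: 1594 × 0.8 = 1275.2, about 1275.
- Shortfall: 1328 − 1275 = 53, and 53 / 1328 = 4.0%.
- Loss that 1594 does cover: 1 − 1328 / 1594 = 0.167.
- Enrolment for 20% on the plan's own chain: 1660, which is 66 more than 1594. That is 83 classrooms of 20, or 84 for an even split.

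**Power after a 20% loss from 1594, at d = 0.3055**

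Effective N is the number analysed divided by the design effect. Power is then read from the two-sample t-test; approximately, it is Φ(d × √(effective N / 4) − 1.96).

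| Loss pattern | Design effect | Effective N | Power |
|---|---|---|---|
| No shortfall (1328 analysed, 20 per class) | 3.907 | 340 | 80.2% |
| Analysed classes still average 20 | 3.907 | 1275.2 / 3.907 = 326.4 | 78.6% |
| Loss within classes, 16 per class | 1 + 15 × 0.153 = 3.295 | 1275.2 / 3.295 = 387.0 | 85.0% |

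The figure of 16 per class is an assumption: 20 × 0.8, with the loss spread evenly over classrooms. At the fixed design effect, the slip costs 80.2 − 78.6 = 1.6 percentage points.

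**The case against.** The best defence is that the slip is outweighed by a conservative choice elsewhere in the same chain. The 20 per class is the enrolled class size (1594 / 20 = 79.7, hence 80 classrooms), and the design effect for 20 is kept after the loss. The losses the article describes concern individual students: codes that cannot be matched within a classroom (Data Matching, Limitations), absence (Survey Collection Procedures), withdrawal (Retention) and missing follow-up surveys (General Issues). It does not anticipate losing whole classrooms. If 20% are lost in that way, the need is 340 × 3.295 / 0.8 = 1400, and 1594 is more than enough. This stands. It limits the consequence, but it does not make 1594 the right answer to the stated step. The word for approximately does not rescue the figure either, since 1594 follows to the unit from exactly 20%.

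A reader might go further and infer two things that the documents do not support.

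- *That 340 is also wrong, because d = 0.30 exactly needs 352 by t-test (350 by normal approximation).* The input actually entered was the 62nd percentile, and 340 is exactly right for that. The 0.30 is 0.3055 rounded. Nor does this bear on whether 1594 leaves 1328, which depends only on the loss step.
- *That power falls to 77%.* That figure needs both unchanged class sizes after the loss and 0.30 in place of 0.3055. On the plan's own input the unfavourable pattern gives 78.6%.

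**Conclusion.** The point holds as a minor arithmetic error in a stated figure. The figure of 1594 does not allow for the 20% loss claimed: it allows for 16.7%, and after a 20% loss it leaves 53 students fewer than the 1328 given as needed. The remainder of the chain is correct on its own inputs.

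It does not show that the trial is underpowered for the loss it describes. With student-level loss, power is about 85%, above the 80% target; only if analysed classes keep 20 students does it fall slightly below, to about 79%. These figures rest on the plan's ICC of 0.153 and d = 0.3055, on lost students adding no information, on equal class sizes, and on no gain from the baseline covariate that the Statistical Analysis section includes.

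**What to change.** Correct the text in two places, the Sample Size section and the Methods paragraph of the Abstract. No extra students or classrooms are needed.

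- State that 1594 students (80 classrooms) allow for a loss of about 16.7% at the fixed design effect of 3.907. If the 20% is to be kept as the basis of that step, the figure is 1660.
- State the power of 80 classrooms after a 20% loss on the plan's own input: about 85% if the loss falls within classrooms (16 per class, design effect 3.295), and about 79% if analysed classes still average 20.
- Optionally, note that the 62nd percentile is d = 0.3055, rounded to 0.30. The 340 itself needs no change.

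The cost is a few sentences. The only loss is that one scenario is now openly reported as just under 80%.
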